## Introduction

More than 1 in 10 births are preterm (<37 weeks gestation),^1^ with survivors at considerable risk of life-long disabilities, including cerebral palsy (CP), intellectual impairment, social/behavioural difficulties and educational disadvantage.^2 3^ The family, health and broader societal costs are estimated at >$26 billion per annum in the USA alone.^4^

CP is a permanent condition of motor dysfunction, is the most common physical disability in childhood, and almost 50% of cases are due to preterm birth.^5^ CP has a higher disability burden than blindness, deafness, severe asthma or diabetes.^6^ Thus, any intervention that reduces the risk of CP among preterm infants, particularly a simple, low-risk, low-cost treatment, would have considerable personal and economic benefits.

Antenatal maternal magnesium sulfate (MgSO_4_) therapy is established as neuroprotective for preterm infants,^7 8^ and is now standard of care in Australia for women at risk of imminent preterm birth <30 weeks gestation.^8^ Meta-analysis of high-quality randomised controlled trials has demonstrated a 29% risk reduction in the rate of CP, and a 40% reduction in substantial gross motor dysfunction for preterm infants exposed to MgSO_4_ before birth.^7^ However, approximately 40% of mothers of preterm infants born <32 weeks gestation in Australia and New Zealand do not receive this treatment, often due to ineligibility or urgent birth.^9^ If the precise neuroprotective component of MgSO_4_ can be identified, there is potential for direct treatment of preterm newborns, with universal accessibility, to prevent neurological sequelae.

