### Sulfate deficiency in the neonatal period following very preterm birth

Infants born <32 weeks gestation (very preterm (VP)/extremely preterm (EP)) will likely rapidly become deficient in sulfate due to three factors: (1) minimal dietary supply of free inorganic sulfate in breast milk (including colostrum),^32^ total parenteral nutrition solutions, and human milk fortifiers; (2) negligible capacity to generate sulfate from sulfur-containing amino acids due to low expression of cysteine dioxygenase gene^14 33^; (3) immature renal function including low expression of SLC13A1, with limited ability to reabsorb filtered sulfate.^15 21 34 35^

Maturation of various physiological systems in the preterm infant accelerates postnatally, for example, surfactant protein production^36^ and renal maturation.^35^ Hence, it is likely that preterm infants rapidly switch on expression of the cysteine dioxygenase and SLC13A1 genes after birth, and thus develop the capacity to generate and retain sulfate within days to weeks.

A pilot study at the lead study site (online supplemental file 1) demonstrated that, as predicted, sulfate concentrations among VP/EP newborns fell rapidly over the first week after birth, before stabilising and increasing thereafter. As VP/EP infants are born during a critical period of brain development, they are likely to be highly vulnerable to adverse effects of hyposulfataemia. This window of vulnerability also coincides with the occurrence of IVH and ischaemia (later manifesting as periventricular leukomalacia (PVL)), both predisposing factors for adverse neurodevelopmental outcome. The pilot study at the lead study site (online supplemental file 1) also showed that antenatal MgSO_4_ largely mitigates the occurrence of very low concentrations in the preterm infant; boosting sulfate to supra-physiological concentrations at birth which then decay to normal or adequate concentrations by which time the infant’s capacity to generate and retain sulfate may have matured. However, common reduced-function variants of renal *SLC13A1* and placental *SLC13A4* sulfate transporter genes may impede the efficacy of antenatal MgSO_4_ treatment to boost fetal sulfate concentrations.

10.1136/bmjopen-2023-076130.supp1Supplementary data

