Given the strong scientific rationale for sulfate as the neuroprotective component of antenatal MgSO_4_, the aim of this study is to test the hypothesis that among VP/EP infants, severity of hyposulfataemia in the first week after birth correlates with adverse neurodevelopmental outcome. The primary outcome is CP, given the findings of the Cochrane meta-analysis of antenatal maternal MgSO_4_ treatment, but as per the recommendations of the Cochrane Review,^7^ other neurodevelopmental outcomes will be studied, including motor delay, cognitive function, language development and social/behavioural difficulties. This is particularly relevant given that animal studies suggest that sulfate deficiency has widespread effects on neurodevelopment, not confined to white matter abnormalities alone.^24 28–30 37^ Furthermore, vascular abnormalities which may be related to sulfate deficiency^15 23^ such as IVH, ROP, capillary haemangiomas will also be ascertained.

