### Secondary aims

To explore changes in plasma sulfate concentrations over time, by correlating with the fractional excretion index (FEI) of sulfate at 1, 3, 7, 14 and 28 days of age, for VP/EP infants exposed to antenatal MgSO_4_ versus unexposed.To explore whether, for VP/EP infants exposed to antenatal MgSO_4_, known loss-of-function variants in the maternal/infant *SLC13A1* or maternal *SLC13A4* genes are associated with lower plasma sulfate concentrations at 7 and 28 days of age.To explore the impact of antenatal, neonatal and genetic factors (including MgSO_4_ dose, FEI sulfate and sulfate transporter gene variants) on neonatal sulfate concentrations within the first 28 days after birth, and to establish a population pharmacokinetic model for sulfate in the VP/EP infant.To explore potential relationships between plasma sulfate concentration in VP/EP infants at 7 days of age and IVH (worst grade during neonatal intensive care unit (NICU) admission), ROP (worst stage in early infancy) or capillary haemangiomas (number and size in infancy).

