### Statistical methods

#### Primary aims 1 and 2

Descriptive statistics will be used to present the antenatal, intra partum, post partum, neonatal and follow-up characteristics, including plasma sulfate and magnesium concentration, of the cohort. Bivariate relationships will be explored between these characteristics and CP and adverse motor/cognitive/language/behavioural outcomes. Mixed-effects regression models will examine the association between plasma sulfate and magnesium concentrations at 7 days of age with adverse outcomes; site will be included as a random effect, with characteristics known to be associated with the outcome from literature and clinical experience, as well as demonstrating an association in bivariate analyses, included as fixed effects. The number of factors included will be restricted dependent on the prevalence of the outcome. Both unadjusted and adjusted effect estimates will be presented, along with 95% CIs, and p values for the primary model examining CP. An a priori subgroup analysis for <28 weeks versus ≥28 weeks will be undertaken.

#### Primary aim 3

Receiver operator characteristic (ROC) curves will be constructed, using CP/motor delay/cognitive delay/language delay/behavioural difficulties as individual outcomes, and the sulfate concentration as the predictor. The area under the ROC curve (AUROC) will be calculated and presented, along with the 95% CIs. The sulfate concentration that results in the best combination of sensitivity and specificity will be calculated (Youden’s index) for each outcome.

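### Covariates for the primary CP model are chosen by association with the outcome, so the rule could admit IVH/PVL, which may follow from low sulfate, and could drop antenatal MgSO4 exposure

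*Protocol article*

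**What the plan says.** Under Statistical methods, Primary aims 1 and 2, the protocol describes "antenatal, intra partum, post partum, neonatal and follow-up characteristics" and examines them against CP one at a time. Fixed effects for the regression are then "characteristics known to be associated with the outcome from literature and clinical experience, as well as demonstrating an association in bivariate analyses". Site is a random effect. The rule ends with a cap: "The number of factors included will be restricted dependent on the prevalence of the outcome". No screening p-value is given, no class of variable is ruled out, and this section forces no covariate into the model. The Sample size section does foresee confounders and names plasma magnesium as one.

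Other sections describe the variables that this rule would act on:

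- **IVH and PVL as predictors.** The section on sulfate deficiency after very preterm birth calls them "both predisposing factors for adverse neurodevelopmental outcome".
- **IVH as a consequence.** The same section lists IVH among "vascular abnormalities which may be related to sulfate deficiency". Secondary aim 4 studies "potential relationships between plasma sulfate concentration in VP/EP infants at 7 days of age and IVH". The IVH and PVL section codes the worst finding over scans on days 5 and 28 and at 34-36 weeks, whereas sulfate is sampled on day 7 ± 1.
- **Antenatal MgSO4.** The Introduction calls it "standard of care in Australia for women at risk of imminent preterm birth <30 weeks gestation" and cites a 29% reduction in CP. The pilot study is said to show that it "largely mitigates the occurrence of very low concentrations in the preterm infant".

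**The concern.** A screen on association with the outcome finds predictors of CP. It does not separate confounders of the sulfate-CP relation from variables that lie on the path between them.

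A variable such as IVH is a natural candidate, because the protocol itself calls it a predictor. If low sulfate contributes to IVH and IVH contributes to CP, adjusting for IVH removes part of the effect under test.

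Antenatal MgSO4 exposure raises sulfate and is believed to lower CP. It is given mainly at the gestations where CP risk is likely to be highest, so its crude association with CP may be masked and it may fail the screen. Day-7 sulfate would then stand in partly for having been exposed. The study exists to learn which component of MgSO4 protects, so the handling of exposure bears directly on its main conclusion.

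**Working it through.** **1. The plan's own figure.** Inputs from Sample size: CP 7%, odds ratio 0.74 per SD, 80% power, two-sided 0.05. The formula for a continuous predictor is N = (1.96 + 0.84)² / [p(1−p)(ln OR)²]. With p(1−p) = 0.07 × 0.93 = 0.0651 and ln 0.74 = −0.301, N is about 1330; the plan states 1324. This reproduction includes no inflation for covariates correlated with sulfate. Expected events are 1324 × 0.07 = 93, or roughly nine terms at ten events per term.

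**2. Can IVH pass the screen?** Prevalence and relative risk are not in the protocol. At an assumed prevalence of 10%, an IVH indicator passes at p<0.05 with probability 32%, 73% or 98% for a relative risk of 1.5, 2 or 3.

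**3. Effect of adjusting for a mediator.** With mediated share m (assumed), the adjusted odds ratio is exp[(1−m) ln 0.74]. Power is Φ(|ln OR| √(1324 × 0.0651) − 1.96), taking the standard error as unchanged.

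| m | Odds ratio | Power |
|---|---|---|
| 0 | 0.74 | 80% |
| 25% | 0.80 | 55% |
| 50% | 0.86 | 29% |
| 75% | 0.93 | 10% |

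A large simulation with IVH as partial mediator agrees in direction: 0.80 without IVH in the model and 0.86 with it.

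**4. Can MgSO4 fail the screen, ignoring gestation?** Inputs from the protocol: about 60% exposed (the Introduction says about 40% are not), relative risk 0.71, CP 7%, N = 1324. CP risk is 0.07/(0.6 × 0.71 + 0.4) = 8.5% if unexposed and 0.71 times that, 6.0%, if exposed, with about 530 and 794 infants. A two-proportion test detects this with probability 41% at p<0.05, 53% at p<0.10 and 66% at p<0.20.

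**5. The same with gestation.** Cohorts of 1324 were simulated with sulfate inert, MgSO4 odds ratio 0.69, exposure 75% below and 30% above 30 weeks (59% overall), and a CP log-odds slope of −0.20 per week. The exposure split and slope are assumed.

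- The crude MgSO4 odds ratio is about 0.9. Exposure passes in 6-10% of cohorts at p<0.05 and in 24-27% at p<0.20.
- With a slope of −0.10 it passes in 20-21% at p<0.05 and 43-48% at p<0.20.
- Across slopes from −0.05 to −0.20 and splits of 75/30, 70/50 and 60/60, at 7% CP, retention at p<0.05 runs from about 5% to 42%.

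**6. Effect of dropping MgSO4.** In the step 5 model, with sulfate 1-2 SD higher in exposed infants (assumed), the gestation-adjusted sulfate odds ratio is 0.94 to 0.89 per SD although sulfate does nothing. The false-positive rate is 8-21% across runs. Adding exposure returns the odds ratio to about 1.00, with 4-6% false positives. When MgSO4 instead acts only through sulfate, the odds ratio is 0.746 with or without exposure in the model.

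**7. Cost of including MgSO4.** With 60% exposed and a difference of d within-group SDs, R² = 0.24d²/(1 + 0.24d²), which is 0.19 for d = 1 and 0.49 for d = 2. Power is Φ(0.301 √(1324 × 0.0651 × (1−R²)) − 1.96), which is 71% and 51%.

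**The case against.** A reader might infer that the rule would admit IVH/PVL, would usually drop MgSO4, and so leaves the primary estimate biased in both directions. The documents do not support that much.

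- **IVH/PVL are not named as covariates.** They are filed under Short-term outcome data, apart from the antenatal and neonatal data, and IVH is itself an outcome in secondary aim 4. Literature, clinical judgement and the cap on factors also stand between a variable and the model. This stands: the rule permits their entry but does not require it.
- **Their place on the pathway is not settled.** The first scan is on day 5, so some IVH precedes the day-7 sample and may mark illness affecting both sulfate and CP. PVL is not in aim 4; the protocol mentions it as an injury arising in the same window. This stands, and it is a reason to fix their role in advance.
- **No screening threshold is stated.** Ignoring gestation, MgSO4 is kept more often than not at p<0.10 and p<0.20. The lowest retention figures need a steep gestation slope and a sharp split in exposure. This stands: at p<0.05 exposure is dropped more often than kept in every setting tried, but a general statement across thresholds is not supported.
- **Bias from dropping MgSO4 is conditional.** If MgSO4 acts only through sulfate, as the study hypothesises, there is none. Plasma magnesium is planned in the model. In a simulation with an assumed weak link between exposure and plasma magnesium, it moved the odds ratio only from 0.91 to 0.92, against 0.99 with exposure included.
- **Unadjusted estimates are also reported.** They limit how far adjustment can hide an effect, but they do not address confounding.
- **A full covariate list may sit in an analysis plan not shown.** That is fair for the list. The selection rule, however, is stated in the article and is what is questioned here.

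**Conclusion.** The point holds in conditional form. The stated rule selects on the outcome and has no safeguard in either direction.

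If IVH/PVL enter and mediate 25-75% of the effect, the odds ratio moves from 0.74 to 0.80-0.93. No figure in the protocol fixes that share.

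If MgSO4 exposure is dropped and acts on CP by a route other than sulfate, an inert sulfate would show about 0.89-0.94 per SD. If it acts only through sulfate, dropping it does no such harm. Retention at p<0.05 is about 41% from the protocol's figures alone and roughly 5-42% under assumed gestation slopes and exposure splits.

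The documents do not show that either event will happen. They show that both are left to a data-driven screen, in a study meant to separate sulfate from the other ways MgSO4 might protect. Because only about nine terms are affordable, the choice of terms matters.

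**What to change.** Replace the bivariate screen with a confounder set named before analysis and sized to the events limit. One example is gestational age, sex, birth weight, multiple birth, antenatal steroids and plasma magnesium, with site as the random effect. With sulfate that is seven fixed terms, and eight if MgSO4 exposure is added.

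Keep IVH, PVL and ROP out of the primary model. Report an IVH/PVL-adjusted result as a labelled sensitivity analysis, noting that IVH seen on day 5 could be a confounder.

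Report the sulfate estimate with and without antenatal MgSO4 exposure as two pre-specified models, and say in advance which is primary. Estimates within exposed and unexposed infants, with the interaction, are optional.

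The change is to wording, since the protocol already collects the MgSO4, gestation and IVH/PVL data. The price is precision: MgSO4 explains part of the variation in sulfate, so the model that includes it could have about 71-51% power at 1324 instead of 80%, if sulfate is 1-2 SD higher in exposed infants (assumed). That trade-off should be stated when the primary model is chosen.

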### Primary aims

To determine whether there is a relationship between plasma sulfate and/or magnesium concentration in VP/EP infants at 7 days of age and formal diagnosis of CP at 2 years corrected age (CA), or absent fidgety movements^38^ at 12–14 weeks CA as a surrogate outcome when formal clinical assessment is unavailable, with subgroup analyses for EP and VP infants.To determine whether there is a relationship between plasma sulfate and/or magnesium concentration in VP/EP infants at 7 days of age and any adverse neurodevelopmental outcome at 2 years CA; motor, cognitive and language scores as assessed by Bayley Scales of Infant and Toddler Development (Bayley III/4^A&NZ^),^39 40^ behavioural difficulties as assessed by Strengths and Difficulties Questionnaire (SDQ),^41 42^ and a composite ‘any moderate-severe disability’, with subgroup analyses for EP and VP infants.To determine the optimal threshold of plasma sulfate and/or magnesium concentration identifying participants with risk of each adverse outcome; CP, motor/cognitive/language delay, behavioural difficulties, thereby identifying a potential plasma sulfate/magnesium target concentration for supplementation. Separate analyses will be performed for each adverse outcome, and for the composite ‘any moderate-severe disability’, along with separate analyses for EP and VP infants.

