## Sample size and statistical analysis

### Sample size

The study was powered for identifying the relationship between plasma sulfate and/or magnesium and the primary outcome, diagnosis of CP (primary aim 1). At the lead study site (MMH), based on audit of data, the CP rate for VP/EP survivors was 7%. The published risk reduction of antenatal MgSO_4_ on CP as per the Cochrane Review of this therapy is 29%.^7^ As such, to determine a clinically significant reduction in the proportion of infants with CP at 2 years CA (7%–5.25%, corresponding to a 30% relative reduction and an OR of 0.74 when sulfate concentration is increased by 1 SD above the mean), and assuming 80% power, a type I error of 0.05 and using plasma sulfate as a continuous predictor, 1324 infants are required. This calculation is based on using logistic regression as the primary analysis technique, and allows for a set of confounders to be included, including plasma magnesium concentration. Allowing for 17% participant loss, including deaths, withdrawals and lost to follow-up, a sample size of 1595 infants will be required.

A sample size calculation for primary aim 2 has not been performed, as the Cochrane Review^7^ was unable to demonstrate a risk reduction effect for intellectual deficits or developmental delay. Cognitive and language delay in VP infants is however much more prevalent than CP, and these outcome measures are continuous variables (standard scores). The sample size calculated for primary aim 1 will therefore be sufficient to detect a clinically significant risk reduction for cognitive/language outcomes if present. Primary aim 3 is predominantly exploratory, and as such a sample size calculation was not undertaken, and p values will not be presented.

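### Primary aim 3 promises thresholds that its method does not cover, and reports each supplementation-target cut-off as a point with no measure of error

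*Protocol article*

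**What the plan says.** The third item under Primary aims in the protocol article reads "To determine the optimal threshold of plasma sulfate and/or magnesium concentration identifying participants with risk of each adverse outcome", and gives the purpose as "thereby identifying a potential plasma sulfate/magnesium target concentration for supplementation". It commits to separate threshold analyses for every adverse outcome, for the composite of moderate to severe disability, and for EP and VP infants.

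The Primary aim 3 paragraph under Statistical methods is narrower. It plans ROC curves for five individual outcomes (cerebral palsy, motor delay, cognitive delay, language delay and behavioural difficulties), "and the sulfate concentration as the predictor". The AUROC is to be presented with a 95% CI. Then, for each outcome, "The sulfate concentration that results in the best combination of sensitivity and specificity will be calculated", using Youden's index. The paragraph does not mention magnesium, the composite, or a split by gestation. The subgroup analysis at 28 weeks appears only in the paragraph on primary aims 1 and 2.

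The Sample size section describes aim 3 as largely exploratory, with no sample size calculation and no p values.

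**The concern.** There are two problems.

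- **The aim and its method do not match.** The method paragraph is specific enough to list five outcomes and one predictor, yet it leaves out one of the two predictors, the composite outcome and the two gestational strata that the aim promises. A reader cannot tell which of these threshold analyses will be run.
- **The planned uncertainty measure is attached to the wrong quantity.** The quantity meant to inform a supplementation target is the cut-off concentration. An interval for the AUROC describes how well sulfate ranks infants; it does not say where on the sulfate scale the cut-off lies. Youden's cut-off is also the point that maximises an index in the same data, so the sensitivity and specificity reported at that point are optimistic.

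At stake is a concentration that could be carried into the design of a supplementation trial as though the data had located it.

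**Working it through.** **Inputs from the Sample size section.** The cerebral palsy rate is 7%. The effect is "an OR of 0.74 when sulfate concentration is increased by 1 SD above the mean". The size statement is "assuming 80% power, a type I error of 0.05 and using plasma sulfate as a continuous predictor, 1324 infants are required", followed by "Allowing for 17% participant loss, including deaths, withdrawals and lost to follow-up, a sample size of 1595 infants will be required".

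**Step 1: reproduce the plan's own number.** For logistic regression on one standardised normal covariate, taking the type I error as two-sided:

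n = (z₀.₉₇₅ + z₀.₈₀)² / [p(1−p)(ln OR)²] = (1.960 + 0.842)² / [0.07 × 0.93 × 0.3011²] = 7.849 / 0.005902 ≈ 1330.

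The plan states 1324, a difference of about 0.4%. For losses, 1324 / 0.83 = 1595.2, against 1595 stated. The design therefore reproduces, and the same inputs can be used for aim 3.

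**Step 2: discrimination implied by the powered effect.** With equal-variance normal distributions, the case-control difference is d = −ln 0.74 = 0.301 SD.

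- AUROC = Φ(d/√2) = Φ(0.213) = 0.584.
- Maximum Youden index = 2Φ(d/2) − 1 = 0.120, with sensitivity and specificity both about 0.56.
- Expected cases: 1324 × 0.07 ≈ 93. The AUROC estimate then has a 95% sampling range of about 0.52 to 0.64.

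**Step 3: sampling behaviour of the cut-off.** Cohorts were simulated from the logistic model with normal sulfate, and the Youden index was maximised over all observed values (4000 cohorts in the base case). Cut-offs are in SD of sulfate.

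| Setting | 95% range of cut-off | Mean apparent index |
|---|---|---|
| Base: n = 1324, 7%, OR 0.74 | −1.04 to +0.77 | 0.165 |
| Commoner outcome, 15% (assumed) | −0.88 to +0.61 | 0.150 |
| Stronger effect, OR 0.50 (assumed) | −0.89 to +0.26 | 0.302 |
| EP-sized stratum, n = 400, 10% (assumed) | −1.30 to +0.96 | 0.195 |
| n = 20,000, 7%, OR 0.74 | −0.55 to +0.29 | 0.127 |
| No association, OR 1 | −1.95 to +1.91 | 0.066 |

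In the base case the true optimum is at −0.13 SD. Repeat runs put the upper limit between +0.70 and +0.77, so the range is about the 15th to the 76th–78th percentile of sulfate. The apparent index exceeds the true one by a factor of 0.165 / 0.119 ≈ 1.39. The range stays wide even at 20,000 infants because the index is nearly flat around its maximum.

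**Step 4: a different shape of effect.** The log-linear model contains no real threshold. The simulation was repeated with a step in risk, matched to give the same case-control difference in mean sulfate (7% cerebral palsy, n = 1324).

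- Step at 0 SD: −0.50 to +0.31, width 0.81.
- Step at −0.5 SD: −0.78 to +0.13, width 0.91 (0.97 in a repeat run).
- Step at −1 SD: −1.18 to +0.15, width 1.33.

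So for a step at −0.5 or 0 SD the width is about 0.8 to 1.0 SD, roughly half the base-case width of 0.77 + 1.04 = 1.81 SD.

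**The case against.** The strongest reply is that the Sample size section labels aim 3 largely exploratory, and the aim itself speaks only of a potential target. Youden's index is a standard choice for such work. Bootstrap intervals and optimism correction are details that a condensed article may leave to an analysis plan, which is not shown here. The AUROC interval, at about 0.52 to 0.64, would already warn readers that discrimination is weak. Much of this stands, and it lowers the weight of the point. It does not remove it: aim 3 is still listed as primary, the cut-off has a stated use, and the mismatch between aim and method is between two explicit texts.

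Three stronger readings are tempting but are not supported.

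- **That the cut-off cannot be located at all.** This depends on the log-linear model. The introduction's rationale is closer to a deficiency threshold, under which the range can be about half as wide.
- **That confounding by gestation will shift or reverse the cut-off.** Antenatal magnesium sulfate is standard of care before 30 weeks and could raise sulfate in the least mature infants. The introduction also says that immature kidneys lose sulfate, which would lower it. The documents fix neither the size nor the direction, and separate EP and VP thresholds would control gestation in part.
- **That magnesium and the composite have been dropped.** The aim still commits to them, so a drafting gap is the more natural reading.

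**Conclusion.** The point holds in a limited form and is worth correcting. The mismatch needs no assumptions: magnesium, the composite and the EP and VP threshold analyses are in the aim and absent from its method.

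The imprecision rests on the plan's own powered effect plus two assumptions, normal sulfate and the shape of the effect. Depending on shape, the 95% range of the cerebral palsy cut-off is from about 0.8 SD wide (a step near the mean) to about 1.8 SD wide (log-linear), with 1.3 SD for a step at −1 SD. In the log-linear case the apparent Youden index is inflated by about 40%. The ranges for the commoner outcome and for the EP stratum use assumed rates and numbers and are illustrative.

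The consequence is limited to how a cut-off may be reported and used. It does not touch the primary regression of cerebral palsy on sulfate.

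**What to change.** Amend the Primary aim 3 paragraph under Statistical methods as follows.

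1. Report each cut-off with a bootstrap 95% CI, resampling pregnancies so that multiples stay together and repeating the search for the cut-off in every resample.
2. Report optimism-corrected sensitivity, specificity and Youden index from the same bootstrap.
3. Run the same analysis for magnesium, for the composite, and for EP and VP infants separately, as the aim states.
4. Describe the cut-offs as hypothesis-generating, and name no potential target where the interval spans most of the observed concentration range.

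A gestation-adjusted ROC curve or an adjusted risk curve could be added as a sensitivity analysis; this is a matter of preference.

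The cost is a few extra analysis runs on data already being collected. The real downside is that the study may be unable to name a target.
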